## 1.0 BACKGROUND AND RATIONALE

---

### Cancer Therapy Background

The paradigms for treating advanced malignancies have drastically changed over the past 60 years. Historically, chemotherapeutic agents have been used to treat numerous types of cancers. Scientists are now attempting to use their growing knowledge of cancer biology to create targeted therapies that are less harmful to benign cells and more deadly to cancer cells. Targeted therapies may be less harmful to the body because they are more specific in their targeting of cancer cells. Although many people receiving conventional chemotherapy still experience “classic” side effects such as nausea, fatigue, hair loss, and an increased susceptibility to infections, thanks to modern techniques, these side effects are no longer universal to all cancer treatments.

Although it began, like so many discoveries, as serendipity, the science of chemotherapy continues to evolve and improve. The inception of modern chemotherapy for treating cancer can be linked to the discovery of nitrogen mustard, a chemical warfare agent developed in the 1940s. Two pharmacologists, Louis Goodman and Alfred Gilman, were recruited by the U. S. Department of Defense to study the potential application of chemical warfare agents for therapeutic purposes. Based upon autopsies of individuals exposed to mustard gas, they “accidentally” discovered profound suppression of white and red blood cells. Together, they hypothesized that this agent could be used to treat lymphoma. Following World War II, a novel approach to treating cancer was investigated by Sidney Farber, a pathologist at Harvard Medical School. He studied the effects of folic acid, a vitamin crucial for DNA synthesis and repair, in children with leukemia and discovered that it stimulated the leukemia cells to divide. This led to the development of a drug that could block this mechanism. Together with collaborators, [name] used methotrexate, an anti-folate drug, to induce remission in children with leukemia. In 1958, this same drug cured a patient with choriocarcinoma, a solid tumor that originates in the placenta. This was the first solid tumor cured by chemotherapy. Seven years later, the investigators James Holland, Emil Freireich, and Emil Frei suggested that, like the treatment for tuberculosis, chemotherapy should be given in combination rather than as a single agent. The goal was to attack the cancer from several different angles. With time, physicians realized that these treatments worked well for small tumors but not for larger ones and started using chemotherapy in combination with surgery. Medical oncologists prescribing chemotherapy regimens soon hit a wall. Despite President Nixon’s declaration of a war on cancer with the National Cancer Act of 1971, patients were still dying of their tumors. Many tumors were found to be resistant to chemotherapeutic agents. In fact, some regimens merely resulted in side effects without providing benefit because the drugs’ aims were too broad. To these drugs, certain benign cells, such as those in the intestine and hair follicles, looked just like malignant ones. In line with President Nixon’s vision, the 1980s and 1990s saw a cancer treatment renaissance. While clinicians made many discoveries, a significant number of treatment trials were being blazed in the laboratory. Scientists began studying the mechanisms underlying cancer cell biology so that they could “snipe” instead of “carpet bomb.” Up to this point, chemotherapeutic agents had been discovered essentially by chance, or by inhibiting the metabolic pathways thought to be crucial to cell division. But with new understanding of the cross-talk within normal cells and cancer cells, chemotherapeutic bullets could be aimed at the signaling networks that were allowing only the cancer cells to proliferate and survive.

The perfect example of such targeted drug development was imatinib mesylate (Gleevec®, Novartis, Pharmaceutical, Basel Switzerland). The use of imatinib in the treatment of chronic myelogenous leukemia (CML) transformed the disease by rapidly changing the median survival from 4 years to more than 20 years.[1] The underlying reasons for this revolution included: 1) the identification of a critical driving molecular alteration, namely *Bcr-Abl*; and 2) the development of a potent and specific *Bcr-Abl* inhibitor, imatinib.[2] It turns out that this small molecule also inhibits *c-KIT*, a tyrosine kinase signaling molecule. What makes *c-KIT* so special is that 90% of Gastrointestinal Stromal Tumors (GISTs) contain an activating *KIT* mutation. GIST is now recognized as the most common sarcoma of the gastrointestinal tract. It is believed that there are up to 6,000 new cases of GIST diagnosed each year in the United States alone. The application of imatinib in the treatment of GIST reflects a major advance in the treatment of all solid tumors with specific molecular targeting. In fact, matching patients to this targeted therapy is solely based upon actionable *KIT* genomic alterations and has clearly led to anti-tumor activity. Imatinib, is now the first-line treatment for metastatic, unresectable, recurrent, and resected high-risk GIST.[3]

Perhaps equally important as having the right drug for the right target was the timing of the targeted therapy; specifically, its administration to patients with newly diagnosed disease rather than advanced disease. Indeed, the response rates of patients with CML that are in blast transformation are only about 15% and all patients relapse; the median survival has increased from 6 months to about 12 months with single-agent BCR-ABL inhibitors.[1] In contrast, with the late use of these inhibitors, median survival of newly-diagnosed CML has increased from 4 years to 20-25 years. Thus, earlier treatment in the disease process has been a transformative change in this hematological malignancy. Until 2009, the same could not be said for any solid tumor. All of the available randomized controlled clinical trials in the treatment of GIST addressed the use of imatinib in advanced (surgically unresectable or metastatic) disease. Whether it was beneficial following earlier in the disease's natural history was unknown. However, in 2009, the American College of Surgeons Oncology Group, published work in "The Lancet" demonstrating the results of the first randomized, controlled trial addressing the role of imatinib in the postoperative period. Interim analysis demonstrated that daily imatinib administered for one year after complete resection of localized GIST provided a reduction in disease recurrence when compared with placebo. Thus, this study clearly demonstrated that postoperative imatinib reduced the rates of early recurrence.[4] This is now standard of care and opened the doors to earlier applications for targeted agents in solid tumors.

Taken together, physicians now take into account the tumor's genomic alteration status, as well as disease progression, possible surgery, and targeted therapy when framing a more multidisciplinary approach to treatment that can include radiologists, pathologists, medical oncologists, and surgeons.

The impact of chemotherapy on the survival of patients with cancers has not yet met the goals set by President Nixon. Cancer remains a major cause of morbidity and mortality in the United States. Unfortunately, many forms of traditional chemotherapy are still ineffective against many cancers. We aim to develop a methodology for targeted, personalized therapies following the GIST and CML paradigms in other types of cancers.

To date, molecular matching has been performed in PREDICT and now WINther, which is IRB approved at UCSD, MD Anderson, and four other sites, will match patients. Therefore, there is precedent for this methodology. Earlier studies reported by [name] and colleagues have shown that this approach can be performed in late stage diseases and have yielded critical insights into personalized cancer therapy.[6, 8] However, the methodology of I-PREDICT is different from what is already in practice. While the protocol for previously treated patients is

similar to the manner in which one might currently treat patients that have previously progressed on other therapies, such an approach is not being utilized early in disease courses of incurable malignancies. Thus, the treatment-naïve patients in our study would not routinely be offered matched therapy at present. As such, the previously described feasibility remains unknown; previously treated patients serve as a control group in our study. While numerous publications on genomic alterations in cancer have been reported, our particular approach is novel. To our knowledge, the only other trials with a similar approach are I-SPY2 in breast cancer and Adjuvant Lung Cancer Enrichment Marker Identification and Sequencing Trials (ALCHEMIST) in early stage lung cancer. More specifically, I-SPY 2 uses novel agents, including phase I drugs, in newly diagnosed breast cancer patients with a risk of relapse of 30% at 10 years; 60% of patients would be expected to be cured in this study. In contrast, our study examines, for the first time, newly diagnosed patients with diseases other than breast cancer. In comparison, we have set a much higher bar for entry—that is patients with  $\geq 50\%$  chance at death at 2 years; these patients have negligible cure rates (**Figure 1**). Meanwhile, ALCHEMIST is supported by the NCI while coordination of the component trials is by the Alliance for Clinical Trials in Oncology and the ECOG-ACRIN Cancer Research Group. The three new NCI trials collectively known as ALCHEMIST aim to identify early-stage lung cancer patients with tumors that harbor certain uncommon genomic changes and evaluate whether drug treatments targeted against those molecular changes can lead to improved survival. Therefore, the NCI is supporting a genomically driven matching trial in patients with earlier stage lung cancer, despite the absence of randomized data. This further confirms that bringing genomically matched therapy to early stage patients with poor prognoses is a strategy of interest for clinical research.

**Figure 1.** Two-year mortality rates for cancers according to the 2014 National Cancer Database (NCDB). Red box indicates eligible patients.

|                                           | Stage III
2-yr Mortality | Stage IV
2-yr Mortality |
|-------------------------------------------|-----------------------------|----------------------------|
| Gallbladder                               | 89.5%                       | 94.8%                      |
| Pancreas*                                 | 86.5%                       | 93.3%                      |
| Liver                                     | 83.0%                       | 93.3%                      |
| Intrahepatic bile duct                    | 79.1%                       | 92.8%                      |
| Esophagus                                 | 70.6%                       | 90.3%                      |
| Bile duct (other)                         | 70.5%                       | 92.2%                      |
| Lung, Bronchus - Non small cell carcinoma | 65.3%                       | 88.7%                      |
| Stomach                                   | 63.9%                       | 90.0%                      |
| Small intestine                           | 37.1%                       | 70.7%                      |
| Ovary                                     | 35.2%                       | 60.8%                      |
| Urinary*                                  | 34.2%                       | 69.9%                      |
| Soft tissue sarcoma including heart       | 31.9%                       | 72.0%                      |
| Melanoma                                  | 24.1%                       | 77.8%                      |
| Breast*                                   | 14.2%                       | 52.1%                      |
| Colorectal                                | 13.4%                       | 58.6%                      |

\* UCSD-specific data; other others are all NCDB cases

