| Statistical Methodology | 
Groups 1, 2, and 3:
 
 
• Determine the feasibility of the genomic-based individualized targeted therapy in patients with incurable malignancies in all patients and in each of the patient groups.
 
• Determine the response rate [(biochemical = tumor markers; radiographic = RECIST)]
 
• Determine the tumor regression rate (%) among groups in order to determine if there is a higher rate in the treatment-naïve groups (i.e., Groups 1 and 2) than in the previously treated group (Group 3)
 
• Determine progression-free survival (PFS) and overall survival (OS)
 
• Determine serious adverse events
 
 
Group 1 and Group 2:
 
 
• The treatment efficacy in the matched cohorts (i.e., Groups 1A and 2A) and the cohort of patients receiving treating physician's choice of traditional systemic chemotherapy [e.g., no drug(s) available for target(s), no insurance coverage for recommended drug(s) = Group 1B and 2B, respectively] will be described.
 
• For the unresectable patients, determine the resectability rate in Groups A and B at 8 weeks and if ever resected.
 
 
Group 3:
 
 
1. For patients in 3A and 3B, we will assess the PFS of the last unmatched therapy (PFS1) versus the PFS of the current therapy (PFS2). We will estimate the percent of patients with PFS2/PFS1 > 1.5.
 
2. The treatment efficacy in the matched cohort (i.e., matched cohort = 3A) and the cohort of patients receiving treating physician's choice of traditional systemic chemotherapy [i.e., no drug(s) available for target(s), no insurance coverage for recommended drug(s) = Group 3B] will be described.
 
 |

|  |  |
|--|--|
|  |  |
|--|--|

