## 2.0 PATIENT ELIGIBILITY

### Inclusion Criteria

Subjects must meet all of the inclusion criteria to participate in this study.

1. Patients with incurable malignancies with  $\geq 50\%$  2-year cancer-associated mortality (as estimated by two physician and where appropriate according to 2014 NCDB data in Figure 1). Diseases include, but are not limited to:

|                                        |                                                 |
|----------------------------------------|-------------------------------------------------|
| Ampullary carcinoma                    | Intrahepatic cholangiocarcinoma (IHCC)          |
| Appendiceal cancer                     | Melanoma                                        |
| Colorectal cancer (CRC)                | Non-KIT GIST (gastrointestinal stromal tumor)   |
| Extrahepatic cholangiocarcinoma (EHCC) | Non-small cell lung cancer (NSCLC)              |
| Esophageal adenocarcinoma              | Ovarian cancer                                  |
| Gallbladder cancer (GBCA)              | Pancreatic ductal adenocarcinoma (PDAC)         |
| Gastric adenocarcinoma                 | Sarcoma (high-grade)                            |
| Head and neck cancer                   | Small bowel adenocarcinoma (including duodenal) |
| Hepatocellular carcinoma (HCC)         | Triple-negative breast cancer (TNBC)            |
|                                        | Urothelial cancer                               |

\* Note: We will limit gastrointestinal malignancies to no more than 65% of the case mix.

2. Patients with cancer of unknown primary or a rare tumor (i.e., fewer than 15 cases per 100,000 per year) with no approved therapies. (Patients in this inclusion criteria must meet all other exclusion and inclusion criteria except inclusion criteria #1)
3. Patients with incurable malignancies, irrespective of 2-year mortality, who, in the opinion of the investigator have no treatment option expected to yield significant clinical benefit."
4. Patients must have at least one of the following for a diagnosis/disease status:
  - a. Unresectable disease
  - b. Metastatic disease
  - c. Medically unfit for surgical resection but with an expected survival of  $> 3$  months, ECOG  $< 2$  and NYHA status  $\leq$  II (refer to status definitions in tables below)

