### **6.1 Study Design**

This is a prospective, open label navigational investigation to evaluate the feasibility of using molecular profile-based evidence to determine individualized cancer therapy for patients with incurable malignancies. This is a non-randomized, histology-agnostic trial. Although there will be a case mix of histologies, we now know that individual histologies are composed of a heterogeneous mix of genomic alterations. It is not clear that one case mix is better or worse than another. Thus, we are testing a strategy of molecular matching that may apply across cancers. All eligible and consented patients will have their tumor tissues/blood genomic profiled by Foundation Medicine's FoundationOne™ genomic analysis. Patients will be stratified into Group 1 (treatment naïve, unresectable/medically unfit for surgery), Group 2 (treatment naïve, metastatic), and Group 3 (prior treated), respectively. Following analysis for genomic alterations, matched therapy, if available, will be recommended by the Study Committee or Molecular Tumor Board. If the patients received the matched therapy, they are designated as in Arm A. Otherwise, if the patients received the unmatched therapy (i.e., treating physician's choice of traditional systemic chemotherapy), they are designated as in Arm B. The study feasibility will be measured by the ability to enroll patients, the acceptable turnaround time and the actionable information obtained from the genomic profiling, and the viability of identifying and delivering the matched therapy. The treatment efficacy will be determined among the patients groups and treatment arms. The safety profile of the treatment will be assessed as well.

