## **6.3 Statistical Methods**

This is a hypothesis-generating trial and not a hypothesis-driven trial. We will collect data prospectively by running concurrent trials (e.g., Groups and Arms) and describing outcomes. We will then analyze the data.

Therefore, the primary statistical analysis is descriptive in nature. Due to the moderate size of the study, the statistical analysis is primarily exploratory and descriptive rather than definitive. The information gathered in this exploratory study will be used for designing future confirmative studies. Summary statistics such as the frequency counts for the categorical variables and minimum, maximum, median, mean, and standard deviation for continuous variables will be computed. In addition, for the analyses of exploratory endpoints, Kaplan-Meier analyses will be computed to estimate the survival rate for time-to-event endpoints. Estimation with both point estimator and 95% confidence estimation for the study endpoints will be provided. Hypothesis testing with appropriate statistical methods will be performed as indicated. For example, Fisher's exact test and chi-square test will be applied to test equal proportion among groups for categorical data such as the response status. Two-sample t-test and Wilcoxon rank sum test will be used to assess the distribution of continuous variable such as the tumor regression percentage between two independent groups. Analysis of variance (ANOVA) and Friedman's test will be applied to assess the distribution of continuous variable among 3 or more groups. Log-rank test and Cox regression model will be applied for comparing the time-to-event endpoints between groups.

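### The planned comparison of tumour regression between treatment-naïve Groups 1–2 and previously treated Group 3 takes no account of tumour type, although the tumour mix is likely to differ between Groups and can bias the result in either direction.

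*Protocol*

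**What the plan says.** **Role of Group 3.** Section 1.1, above Figure 1, says that "previously treated patients serve as a control group in our study". The sentence opens with feasibility. The Study Summary (Statistical Methodology) goes further and compares regression among Groups to "determine if there is a higher rate in the treatment-naïve groups (i.e., Groups 1 and 2) than in the previously treated group". Section 1.3 lists higher eight-week regression in treatment-naïve patients among the study hypotheses.

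**Analysis.** Section 6.3 says that the two-sample t-test and Wilcoxon test "will be used to assess the distribution of continuous variable such as the tumor regression percentage between two independent groups". ANOVA or Friedman's test is named for three or more groups, and Fisher's exact or chi-square tests for response. Section 6.5 repeats this. Sections 6.4 and 6.6 set a one-sided 10% level without multiplicity adjustment. They plan multivariate adjustment for prognostic factors only for PFS and OS, in the bullet on historical controls, and name no factor.

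**Case mix.** Section 6.1 calls the trial histology-agnostic and says "It is not clear that one case mix is better or worse than another". Section 2.1 adds: "We will limit gastrointestinal malignancies to no more than 65% of the case mix".

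**Eligibility.** The bar is 50% or more two-year mortality. The Figure 1 caption says "Red box indicates eligible patients". Section 2.1 applies the bar through physicians' estimates and "where appropriate according to 2014 NCDB data in Figure 1". Criterion 3 admits "Patients with incurable malignancies, irrespective of 2-year mortality", and criterion 2 exempts unknown primaries and rare tumours from the bar.

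**The concern.** A comparison of treatment-naïve with previously treated patients is meant to show whether matching earlier in the disease gives more regression. If the two sides hold different tumour types, and types differ in how much they regress, a crude test mixes the type effect with the timing effect. The protocol states its tests and gives a reason for setting histology aside, so this is not merely a detail left to an analysis plan. The affected result is one of the study's listed hypotheses, and Section 1.3 says the study's results should inform later randomised trials. Tumour type alone could make earlier matching look better than it is, or hide a real advantage.

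**Working it through.** **Step 1: the plan's own figure.** The protocol gives no power or sample size for the Group contrast. Its one response-rate power figure, 79% for 0.25 v 0.05 with 30 v 45 patients, concerns Arm A v Arm B. It reproduces at 79.6% (normal approximation with continuity correction) and does not bear on this point.

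**Step 2: does the tumour mix differ?** Count the Figure 1 rows at or above 50%.

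| Column | Rows ≥50% | Boundary values |
|---|---|---|
| Stage III | 8 of 15 | lowest passing 63.9% (stomach), next below 37.1% (small intestine) |
| Stage IV | 15 of 15 | lowest 52.1% (breast) |

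The eight types are gallbladder, pancreas, liver, intrahepatic bile duct, oesophagus, other bile duct, non-small cell lung and stomach. Under Section 3.2, Group 1 is treatment-naïve and unresectable or unfit, Group 2 is treatment-naïve and metastatic, and Group 3 is previously treated and metastatic or unresectable. Reading Group 1 as the Stage III column is an inference. Group 2 faces the same Stage IV column as metastatic Group 3 patients.

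Unweighted mean Stage IV two-year mortality is 91.9% for the eight types (range 88.7–94.8%) and 66.0% for the other seven (52.1–77.8%). Prognosis therefore differs by type. The documents give no regression or response rates by type.

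**Step 3: assumed inputs.**
- Share of patients in the eight types: 80% of Groups 1–2, 55% of Group 3. If Group 1 came wholly from the eight types and Group 2 had Group 3's 55%, an even split would give 0.5 × 1 + 0.5 × 0.55 = 77.5%.
- Difference in regression between the eight types and the rest: δ = 0.3 to 0.5 SD.
- No true effect of earlier matching.
- Sizes: (a) matched patients at the protocol's expected 30 per Group, so 60 v 30; (b) evaluable patients, 70 v 83.

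For (b), Group 3 accrual over 30 months is 12 × 4 + 18 × 5 = 138. For Groups 1–2 it is 12 × 2 + 18 × 3 = 78 if the stated rate is joint, or 156 if it is per Group, with midpoint 117. Section 3.2 expects 50–70% to be potentially actionable, and 60% gives 0.6 × 117 ≈ 70 and 0.6 × 138 ≈ 83.

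**Step 4: error of the crude test.** The spurious shift is (0.80 − 0.55) × δ = 0.075 to 0.125 SD. Ignoring the small extra variance from mixing types, the chance of declaring Groups 1–2 better is approximately Φ(−1.2816 + shift / √(1/n₁ + 1/n₂)).

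- 60 v 30: √(1/60 + 1/30) = 0.2236. Shift/SE = 0.335 to 0.559, so error = Φ(−0.946) to Φ(−0.723) = 17% to 23%.
- 70 v 83: √(1/70 + 1/83) = 0.1623. Shift/SE = 0.462 to 0.770, so error = Φ(−0.819) to Φ(−0.511) = 21% to 30%.

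Simulating the Wilcoxon test gives 17–23% and 21–29%. Allowing for simulation noise and the approximation, the ranges are about 16–24% and 20–31%. The van Elteren test, stratified on the two classes, stays at about 10% throughout.

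**Step 5: the other direction.** If the eight types regress less (δ = −0.3 to −0.5), the same formula gives 5% to 3% for 60 v 30 and 4% to 2% for 70 v 83. The crude test is then too conservative and loses power for a real advantage.

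**Step 6: a milder imbalance.** With 70% v 55%, the shift is 0.15 × δ = 0.045 to 0.075 SD. Error is Φ(−1.2816 + 0.201) to Φ(−1.2816 + 0.335) = 14–17% for 60 v 30, and Φ(−1.2816 + 0.277) to Φ(−1.2816 + 0.462) = 16–21% for 70 v 83. With equal mixes, or with δ = 0, it is 10%.

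**The case against.** The protocol calls the study descriptive and hypothesis-generating, offers its tests as examples, and says that results need confirmation. An unseen analysis plan could name stratification factors. This lowers the stakes, but it does not remove a directional contrast with a stated significance level, or the stated reason for setting histology aside.

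Several stronger readings are tempting, and the documents do not support them:

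- *Eligibility makes the mix differ by rule.* It does not. Figure 1 guides only in part, criteria 2 and 3 bypass the bar, the disease list is open, and Section 1.3 also counts locally advanced or metastatic disease as high risk. Only Group 1 is narrowed, and its share of the 150 treatment-naïve patients is not given.
- *Figure 1 refutes Section 6.1.* Figure 1 shows mortality, not regression. The Section 6.1 sentence follows a remark on genomic heterogeneity within histologies and makes no claim of equal prognosis. What can be said is that the sentence is too weak to justify unadjusted Group contrasts.
- *The gastrointestinal cap forces the other Groups apart.* It applies to the whole case mix, so it does not balance the Groups, but it hardly separates them either. With an assumed 75 all-gastrointestinal Group 1 patients among 1150 at the cap, the remainder could still be (747.5 − 75)/1075 = 62.6% gastrointestinal.
- *The error could exceed 50%.* Under the same assumptions, 150 v 1000 patients gives roughly 32–54%. Those are enrolment ceilings, and under Section 1.2 patients without actionable alterations leave the study with only basic data captured.

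**Conclusion.** The point holds for the regression contrast of Groups 1–2 with Group 3, and for any response comparison between these Groups. The named tests ignore tumour type, and the stated adjustment does not reach these endpoints. A difference in tumour mix is likely but not guaranteed. Under the assumed 80% v 55% mix and a 0.3–0.5 SD difference favouring the eight types, the nominal 10% error is about 16–24% (60 v 30) or 20–31% (70 v 83), against about 10% when stratified. These figures illustrate sensitivity and do not predict the trial's result.

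A reader might infer that case mix would favour earlier matching. The documents do not fix the direction: the eight types have the higher mortality, so for survival the mix would tend to hide a benefit, and for regression nothing is given by type. Nor does the point show that the PFS and OS comparisons ignore tumour type. They have an adjustment whose factors are unnamed. It does not extend to the share of patients matched, because feasibility is judged within each Group and no formal contrast of it is planned.

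**What to change.** In the Study Summary and Sections 6.3, 6.5 and 6.6:

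1. Stratify the Groups 1–2 v Group 3 contrasts by tumour type: a van Elteren test for regression and a Mantel-Haenszel difference with 95% confidence interval for response. Report crude results alongside.
2. Define the strata in advance, for example Figure 1 rows where both sides have patients, otherwise the eight types passing at Stage III against the rest. State where listed types absent from Figure 1, such as head and neck, and unknown primaries belong.
3. Name tumour type among the prognostic factors for PFS and OS.
4. Qualify the Section 6.1 sentence on case mix so that it does not serve as a reason for unadjusted Group contrasts.

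The cost is analysis wording only. Tumour type is already recorded, including for patients with no actionable alteration. Strata present on only one side contribute nothing to the stratified test. Stratifying also leaves other differences between naïve and previously treated patients in place, so the contrast remains exploratory.
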